**Flow diagram of participants.**

### Sample size

We use the improvement of MMSE scores as the main effect indicators to estimate the sample size. Sample size calculations are performed to determine the number of participants needed to detect effect sizes. Based on the similar papers reported before [38–40] and our preliminary data indicates the mean with SD of the MMSE scores were μ1 = 2.7, μ2 = 5.9, μ3 = 3.7, μ4 = 6 in the CG, EG1, EG2, EG3 respectively, with the SD *σ* = 5.2. To detect 4.6 mean differences among the groups at end of interventions, k represents of the number of groups which is 4 in this trial. About 50 individuals per group will be calculated according to the formula:

With a type I error of 5% (α = 0.05) and 90% power (β = 0.10). Estimating a 20% dropout rate during the study, a minimum of 240 total participants is needed to reach the target 60 participants per group.

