**Table 1 Tab1:** **Trial processes chart**

Items	Before enrollment	Intervention period 1	Outcome assessment 1	Intervention period 2	Outcome assessment 2	Intervention period 3	Outcome assessment 3
	-2-1(week)	1-4(week)	5(week)	5-8(week)	9(week)	9-12(week)	13(week)
Inclusion criteria	×						
Exclusion criteria	×						
Informed consent	×						
Baseline	×						
Randomization and allocation	×						
Intervention		×		×		×	
Mini-mental status examination	×		×		×		×
Montreal cognitive assessment	×		×		×		×
Functional independence measure scale	×		×		×		×
Adverse events		×		×		×	
Reasons of drop-out and withdrawals		×		×		×	

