### Outcome assessment

This study will run for 12 weeks and cognitive function will be assessed by neuropsychological measurement scales which include Mini–mental state examination (MMSE), Montreal Cognitive Assessment (MoCA), Functional Independence Measure Scale (FIM) at baseline and again at 4, 8 and 12 weeks (within a time window: +/- 3 days). All outcomes will be measured by several experienced assessors who are blinded to the randomization group after the baseline visit in the Evaluation Department of Rehabilitation Hospital Affiliated to FJTCM.

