### Patient safety

Adverse effects attributable to the RehaCom therapy may include mental fatigue or headache. Symptoms usually resolve in patients as they progress with therapy and become more familiar with it [33]. Acupuncture may cause discomfort or bruising at the sites of needle insertion, nausea, or feeling faint after each treatment.

During the trial, all unexpected adverse events (AEs) will be observed in detail and documented in CRFs. All AEs reported should be analyzed regardless of the investigators’ assessments of causality. If serious adverse events happen, the researchers should report to the PL and ethics committee immediately, who will make a decision on whether the participant needs to withdraw from the study.

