### Statistical analysis

All allocated subjects will be analyzed with the available data, i.e. on the basis of the intention-to-treat (ITT). A significance level of 95% (two sided p-values alpha < 0.05) will be used. After examining the data for normality (Kolmogorov-Smirnov test) the outcome measures will be analyzed using ANOVA (assuming normal distribution) or Kruskal-Wallis (non-parametric). Demographic characteristics and other baseline values will be described using descriptive statistics for each group. Significant group interactions will be analyzed post-hoc. We will use the Bonferroni method to appropriately adjust the overall level of significance for multiple outcomes.

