### Quality control

A trained RA will explain to each participant the nature of the study, its purpose, the procedures involved, the expected duration, the potential risks and benefits and any discomfort it may entail. Patients or their legal guardians will receive an information letter about the study and there will be no time limit for them to consider implications, ask questions, and respond to the invitation to participate. Participants will be informed that they are free to withdraw from the treatment under study at any stage for any reason without any consequences.The participants screening must according to the inclusion and exclusion criteria. If they meet the inclusion criteria and not meet the exclusion criteria, this procedure will pass. On the contrary, the disqualified participants will be excluded, and the researchers will record the number and the reasons.The random allocation sequence will be produced by an independent statistician via the statistical software SAS 9.1. The project manager allocates the participants according to the random allocation sequence, and it must be deposited for safe keeping ensuring nobody else knows. The cessation of blinding will take place only after all the trial is completed.The missing data should not appear in the CRFs of the missing data in principle. If any missing data appears, researchers should find out whether it is missed in the raw data. If it is missed when loading into database, it should be reloaded. If the missing data affects outcome measure, the participant will be rejected.To ensure that treatments are of a high standard and delivered in accordance with the trial protocol, clinicians involved in assessments, treatment or training will have to provide proven record of at least three year of clinical experience and certified training or education in related fields of rehabilitation or research. The needling will only be performed by professional physicians with specific training in TCM and a minimum of five years of experience. They will participate in a two-day training in the standard operating procedures (SOPs) provided by the author of the manualized protocol and the standard operation videos. In this training the protocol will be explained and practiced on each other during exercises and role-plays. The therapist in the control condition will receive no extra training. In addition, all treatments provided to patients will be carefully recorded in the CRFs.Blinding of study personnel in research projects is a main quality criterion of a study [43]. Although patients, investigators, and therapists administering treatment will not be blinded, those assessing the patients for primary and secondary endpoints will be blinded to patient treatment assignment. The investigators, therapists and assessors are different people. Patients will be told not to talk to the examiner about the group allocation or therapy content during the post-intervention assessments.To maintain the quality of this trial, monitoring will be conducted by the PL located in the Rehabilitation Hospital Affiliated to FJTCM. Investigators can also be convened to discuss practical issues that might be encountered, such as dealing with serious adverse events, revising the protocol, and addressing certain important issues that might be raised by investigators and participants.

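### The missing-data rule under Quality control removes participants whom the Statistical analysis section says will be analysed by intention to treat

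*Protocol article*

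**What the plan says.** The Statistical analysis section of the protocol article defines the analysed population: "All allocated subjects will be analyzed with the available data, i.e. on the basis of the intention-to-treat (ITT". It names no other analysis set.

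The Quality control section deals with missing data in the case report forms. The researcher first checks whether the value is missing in the raw data. For a value lost at data entry, the instruction is: "If it is missed when loading into database, it should be reloaded". The next sentence is: "If the missing data affects outcome measure, the participant will be rejected". The word for removal is not defined.

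Three other places bear on how often the rule would apply. Outcome assessment schedules MMSE, MoCA and FIM "at baseline and again at 4, 8 and 12 weeks (within a time window: +/- 3 days". The Sample size section plans for loss: "Estimating a 20% dropout rate during the study". Table 1 already has a row for "Reasons of drop-out and withdrawals".

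**The concern.** Take a participant with MMSE scores at weeks 4 and 8 and none at week 12, or one with a week 12 score and a missed week 4 visit. Under Statistical analysis the person stays in the allocated arm and the existing scores are used. Under Quality control the person goes, together with those scores. The phrase about available data does not reconcile the two rules, because the Quality control sentence removes the participant and not merely the missing value.

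What is at stake is which population the results describe. A set of participants with complete outcomes is formed after randomisation by what happened later. Patients and therapists know the allocation (Blinding), and patients are "free to withdraw from the treatment under study at any stage for any reason without any consequences", so missingness could differ between arms. As the article stands, either population could be reported as the planned one.

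**Working it through.** **1. Do the two sentences conflict?** The sentence about reloading already deals with values lost at data entry. What remains for the rejection sentence is a score that was never taken. Screening failures are handled in a separate, earlier step of the same section. The sentence therefore falls on randomised participants with a missing MMSE, MoCA or FIM score, whom the Statistical analysis section keeps.

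**2. The plan's own sample size.** Inputs from the Sample size section: means 2.7, 5.9, 3.7 and 6.0; SD 5.2; four groups; alpha 0.05; power 90%.
- Grand mean = (2.7 + 5.9 + 3.7 + 6.0)/4 = 4.575.
- Sum of squared deviations = 3.5156 + 1.7556 + 0.7656 + 2.0306 = 8.0675.
- Noncentrality for n per group = n × 8.0675/5.2² = n × 8.0675/27.04.
- One-way ANOVA power from the noncentral F distribution with 3 and 4(n − 1) degrees of freedom: 0.903 at n = 49 and 0.910 at n = 50. The stated figure of about 50 per group is reproduced.

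**3. Expected dropout.** 0.20 × 240 = 48, or 12 per arm. This leaves 240 − 48 = 192, or 48 per arm, where ANOVA power is 0.897.

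**4. Week 12.** A participant who drops out before week 12 has no week 12 MMSE. An available-data analysis cannot use that person at week 12, and the rejection rule removes the same person. For these 48 the two rules agree, and both leave 192. The sets differ only for participants who have a week 12 MMSE and a gap elsewhere.

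The article gives no rate for such gaps. Assumption: each of the week 4 and week 8 visits is missed independently with probability q among the 192. The share with at least one gap is 1 − (1 − q)².

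| q | Share with a gap | Removed of 192 | Left per arm | ANOVA power |
|---|---|---|---|---|
| 0 | 0 | 0 | 48.0 | 89.7% |
| 1% | 1.99% | 3.8 | 47.0 | 89.0% |
| 2.5% | 4.94% | 9.5 | 45.6 | 87.9% |
| 5% | 9.75% | 18.7 | 43.3 | 86.0% |

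This counts whole missed visits only. A gap on a single scale at an attended visit would add to the number removed.

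**5. Weeks 4 and 8.** Here the rule also discards scores that dropouts did provide. Assumption: the 48 dropouts are spread evenly, 16 before each of the three post-baseline assessments.
- Available data at week 4: 240 − 16 = 224, or 56 per arm. At week 8: 240 − 32 = 208, or 52 per arm.
- Under the rejection rule: 48 per arm at both visits.
- Standard error of a pairwise difference = 5.2 × √(2/n): 0.983 at 56, 1.020 at 52 and 1.061 at 48.
- Ratios: 1.061/0.983 = 1.080 at week 4 and 1.061/1.020 = 1.041 at week 8.
- Completed post-baseline visits discarded: 16 × 0 + 16 × 1 + 16 × 2 = 48. The extremes are 0 (all leave before week 4) and 48 × 2 = 96 (all leave after week 8).

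For simplicity, step 5 applies the planning SD to every visit and ignores the further gaps considered in step 4.

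**The case against.** The rejection sentence sits in a garbled run of database checks and its key word is undefined. Analysis sets are commonly set out in a full protocol or analysis plan, and neither is shown, so the rule might have been meant for a secondary set. That is possible, and exclusion from every analysis is the natural reading rather than a stated one. But nothing in the article confines the rule in that way, and a later document could only choose between two rules that this one states together.

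The second objection concerns size, and it largely stands. A reader might infer that the rule shrinks the main comparison from 240 to 192. It does not. The sample size is set for the end of the interventions, where the 48 dropouts have no score under either rule, and the 20% allowance already absorbs that loss: 48 per arm gives 89.7% power against the planned 90%. The further loss at week 12 rests on assumed gap rates, and the week 4 and week 8 figures concern intermediate visits.

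A reader might also infer that serious adverse events feed the rule, because Patient safety describes the project leader and ethics committee as those "who will make a decision on whether the participant needs to withdraw from the study". The article does not support this. It does not say that assessments stop or that scores are discarded after such a decision, and the phrase may be loose wording for stopping treatment.

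**Conclusion.** The contradiction is real and needs correcting. For a participant with partial outcome data the two sections prescribe opposite handling, and following Quality control as written gives up the intention-to-treat set. The main harm is to the definition of the analysed population, through exclusions caused by events after randomisation. No size or direction of bias can be derived from the article, and it may be small.

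The calculable cost is limited. At week 12 it is about 4 to 19 of 192 participants and 0.7 to 3.7 points of ANOVA power, if 1% to 5% of completers miss each earlier visit. At weeks 4 and 8 standard errors are about 8% and 4% larger, if dropout reaches the planned 20% and is evenly spread. The power figures are for the overall four-group ANOVA at the planning means and SD.

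**What to change.** In Quality control, delete the sentence that rejects the participant and put in its place: *A missing outcome score is recorded with its reason; the participant stays in the allocated arm and is analysed with all available scores.* The instruction to reload values lost at data entry stays, and Patient safety needs no change.

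The cost is one sentence. Table 1 already provides for recording reasons for drop-out and withdrawal, so only the reason for an isolated missed score is new. The downside is that the numbers analysed will differ between visits and must be reported for each. The article gives the trial status as recruiting and says the allocation code is disclosed only after the statistical analysis, so the change can be made before results by arm are known.

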
### Ethics issue

This study is conducted in accordance with the *Declaration of Helsinki*. All participants will be fully informed about the trial, and will sign the written informed consent form prior to participation. The trial is approved by the Ethics Board of the Rehabilitation Hospital Affiliated to FJTCM (2013KY-004-02).

## Discussion

The study is a single-blind, randomized controlled trial of 2 × 2 factorial design mainly to evaluate the synergistic effect of acupuncture and RehaCom cognitive training in patients with cognitive disorders caused by stroke. The trial is sponsored and financially supported by the Program of International Science and Technology Cooperation (No. 2011DFG33240), which is the most important projects to promote national S&T innovation capabilities based on international cooperation.

Cognitive impairment is a condition characterized by mental deficits. Up to 75% of stroke survivors may be considered to have cognitive impairment [8]. These disorders severely limit individual autonomy for successful reintegration into family, work and social life [4]. Despite a high prevalence of post-stroke cognitive impairment, therapeutic possibilities are still limited. So far, complementary or alternative therapies seem to have some positive effect in the post-stroke cognitive impairment (e.g. acupuncture [17, 40] and computer based cognitive training [56]). But, improvements in cognitive function tend to be modest. Besides, currently there is not enough evidence for acupuncture [57] or computer-assisted cognitive training [56] based on strict clinical trial of evidence-based medicine (EBM) because of the poor quality of current studies, for example, small sample size, no description of methods for randomization, no standardized acupuncture protocol, no strict quality control which may lead to performance bias, and so on.

Besides, the cognitive impairment after stroke is so complexity that one single treatment cannot resolve effectively. Additionally, the effects of acupuncture and RehaCom cognitive training have not been systematically compared, nor has the possibility of a synergistic effect of combination of the two therapeutic modalities been evaluated. Due to the acupuncture focus on the global cognitive function from the holistic conception of TCM, while the RehaCom cognitive training concerns the specific impaired cognitive functions which need to be trained from the viewpoint of symptomatic treatment. So, we believe that the interaction of multiple therapeutic strategies (the combination of acupuncture and RehaCom cognitive training) to produce an effect greater than simply the sum of the individual effects of each intervention if they were used separately. Nonetheless, the convincing evidence is still lacking. Therefore, our trial aims to clarify these issues and hopefully provide a more conclusive answer to the questions by the means of randomized factorial controlled trial.

We used cognitive abilities screening scales includes MMSE, MoCA and FIM as the outcome measures in order to track changes in the functional status over the 12-week interventions period. The MMSE [49] is a global measure of cognitive function that has been used extensively both as a diagnostic tool for dementia screening as well as a cognitive outcome measure for gauging the efficacy of the cognitive alterations, for example [58, 59].The MoCA was designed as a rapid screening instrument for mild cognitive dysfunction, which has been found to have high sensitivity and specify for the detection of mild cognitive impairments in various neurological disorders (e.g. Stroke [60]). The FIM was designed to assess disability based on the International Classification of Function (ICF). It is a useful measure of physical and cognitive disabilities in patients with AD and VaD which may reflect global cognitive function [54]. Therefore, they can be a comprehensive neuropsychological test battery to monitor the general cognitive alterations which can reach a more reliable conclusion.

The biggest limitation of this protocol is that it is not double-blinded. However, the outcome assessors and statistical analysts will be blind to the intervention to decrease possible bias to ensure the quality of this trial. The study also lacks long-term follow-up and evaluation. The 12-week intervention period reflects what is done in actual clinical practice and is long enough to test whether a rehabilitation modality is effective in the short term and whether the efficacy is sustained during the follow-up period.

In conclusion, the results of this trial are expected to clarify the synergistic effect of acupuncture and RehaCom cognitive training on cognitive dysfunction after stroke. Furthermore, to confirm whether combined or alone of acupuncture and RehaCom cognitive training, are more effective than conventional treatment in the management of post-stroke cognitive dysfunction.

### Trial status

Ongoing recruitment.
